### 2.11. Randomization and blinding

After baseline measurement, participants will be randomized 1:1:1 to the power cycling group, quadriceps group or control group using simple randomization. A table of random numbers will be produced using the computer soft SPSS (V21.0). Write the random number assigned to each group on a piece of paper and place it in an opaque envelope. Based on the order in which participants were enrolled, an independent biostatistician will randomly distribute envelopes to participants. Physicians and physiotherapists will receive standardized training prior to the start of the study and will be randomly assigned to three groups during the trial. Participants won’t be blinded because of the nature of the intervention; instead, they will only know their own grouping. Evaluators, statisticians, and data managers will be blinded during the trial.

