### 2.4. Participants

We will recruit 72 patients with KOA. Participants’ inclusion criteria are: age ≥ 50 years with KOA, confirmed radiographically (Kellgren–Lawrence grade I–III), with 2021 Chinese Orthopedics Association guidelines for diagnosis and treatment of KOA clinical criteria^[39,40]^; knee pain (previous week) score of 3 to 6 on a numerical rating scale (NRS); able to use a smartphone to send messages and video calls; and able to communicate in Mandarin and understand Chinese characters.

Exclusion criteria are: having rheumatoid arthritis, gout or severe osteoporosis; preparing for knee replacement, other knee surgery in the next 6 months or knee surgery in the past 6 months; history of falls or fractures within the past 6 months; cancer; dementia or severe cognitive impairment; mental illness; diagnosis or suspicion of other conditions that limit exercise (e.g., stroke, heart failure, severe anemia, etc.); hypertension and diabetes not regularly medicated and monitored; other health problems that prevented them from participating in the project; and unable to sign informed consent.

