### 2.9. Sample size

The calculation is carried out according to the standard for the sample size of noninferiority trials and the unified standard for clinical trial reporting.^[38,56]^ Based on the degree of reduction in WOMAC pain scores was used as an index to assess the improvement in symptoms of KOA with each type of exercise. The literature was reviewed to obtain the means and standard deviations of changes in pain scores in the three groups of patients with KOA,^[42,57]^ The sample content estimate formula shows that, for a significance level of 0.05 and a yielding power of 90%,

$$\begin{array}{l} n=\varphi^{2}\left[\sum_{i=1}^{k}S_{i}^{2}/k\;\right]/\left[\sum_{i=1}^{k}{\left({\bar{X}}_{i}-\bar{X}\right)}^{2}/\left(k-1\right)\;\right]\; \end{array}$$

the sample size consists of 20 participants in each group. With a 20% dropout rate taken into account, each group needs 24 enrolled participants.

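### Simple randomisation of 72 participants does not secure the planned 24 per arm, and the envelope sentence is contradictory about whether the generated sequence decides allocation.

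*Protocol article*

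**What the plan says.** All references are to the protocol article.

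- **Planned size.** Section 2.9 starts from "the sample size consists of 20 participants in each group" and continues: "With a 20% dropout rate taken into account, each group needs 24 enrolled participants". Section 2.4 fixes the total: "We will recruit 72 patients with KOA". Three arms of 24 make exactly 72, so the total has no slack.
- **Allocation method.** Section 2.11 (Randomization and blinding): "participants will be randomized 1:1:1 to the power cycling group, quadriceps group or control group using simple randomization". No blocking, stratification or minimisation is mentioned.
- **Implementation.** The same section has a random-number table produced in SPSS, with assignments placed in opaque envelopes. It then says that, following the order of enrolment, "an independent biostatistician will randomly distribute envelopes to participants". Randomisation comes after baseline measurement.

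**The concern.** There are two separate problems.

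First, the sample size section counts on equal arms, while the randomisation section names a method that leaves arm sizes to chance. This is not a detail left to a fuller document: the article names the method. Section 2.1 aims to compare the two exercise arms directly and to compare them with control, so each pairwise contrast matters, and a contrast involving a small arm loses precision.

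Second, the envelope sentence describes two different procedures. If envelopes follow enrolment order, the generated sequence determines who gets which arm and can be checked afterwards. If they are picked at random, the draw determines it and the table does not. Participants know their arm and the primary outcome is self-reported, so the article should be clear about which procedure applies.

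**Working it through.** **Inputs from the document.** Total 72; three arms at 1:1:1; simple randomisation; 20 evaluable per arm; 20% dropout; 24 enrolled per arm. For the error rates, section 2.9 says "for a significance level of 0.05 and a yielding power of 90"%.

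**Inputs not given.** On the means and SDs, section 2.9 says only: "The literature was reviewed to obtain the means and standard deviations of changes in pain scores in the three groups". The figures themselves are not stated, so the 20 per arm cannot be re-derived and the power figures below need an assumed effect.

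**Step 1: the plan's own figure.** 20 × (1 + 0.20) = 24, and 3 × 24 = 72. The stated figure is reproduced. With 20% loss, 24 enrolled leave 24 × 0.80 = 19.2 evaluable, slightly under 20 even when arms are perfectly equal. That small shortfall comes from the inflation rule and not from the randomisation.

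**Step 2: arm sizes under simple randomisation.** The three arm sizes follow Multinomial(72; 1/3, 1/3, 1/3). Each arm has mean 24 and SD √(72 × 1/3 × 2/3) = 4.0.

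P(24/24/24) = 72! / [(24!)³ × 3⁷²] = 0.0114.

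Summing the exact probabilities over all splits gives:

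| Event | Probability |
|---|---|
| Exactly 24/24/24 | 1.1% |
| At least one arm below 24 | 98.9% |
| Smallest arm 19 or fewer, before any dropout | 38% |
| Largest minus smallest arm 8 or more | 53% |
| Largest minus smallest arm 10 or more | 35% |

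The expected smallest arm is 19.9 and the expected largest is 28.2.

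**Step 3: power of a pairwise contrast.** Assumptions: a two-sided t-test at 0.05, an effect that gives exactly 90% power at 20 v 20 (standardised difference about 1.05), and 80% retention in every arm. The noncentrality is d × √[n₁n₂/(n₁ + n₂)], with n₁ and n₂ the retained numbers.

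- Balanced, 24 v 24 enrolled (19.2 v 19.2 retained): 88.7%.
- Averaged over all simple randomisations: 87.8%, a mean loss of about 1 point.
- At least one of the three contrasts below 85%: about 43% of draws.
- At least one of the three contrasts below 80%: about 5% of draws.

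**Step 4: power of the three-group test.** With a noncentral F calibrated to 90% at 20/20/20 and the same retention, power is 88.6% at 24/24/24 and averages 87.9% under simple randomisation. In a bad draw of 28/28/16 with control smallest, it is about 79% if the two exercise arms are equal and about 84% if the three means are equally spaced.

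**Step 5: the envelope sentence.** One clause ties the hand-out to enrolment order and the other makes it random. A third possibility is a random draw from a fixed stock of 24 envelopes per arm. That would equalise the arms, but it would not be simple randomisation and the article does not say it.

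**The case against.** The strongest reply is that simple randomisation is valid and unbiased, and is the least predictable scheme there is. Chance inequality of arm sizes does not bias the comparison, and the average power loss is about 1 point. A larger arm partly offsets a smaller one: 20 v 28 still has about 88% power under the assumptions above. The 24 per arm is a planning figure from a three-group formula and not a condition of validity. All of this stands, and it limits the point to avoidable inefficiency in unlucky draws.

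Three stronger readings are tempting, and the article does not support them.

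- **Concealment is broken and selection bias follows.** The article states opaque envelopes, an independent biostatistician who hands them out, and randomisation after baseline measurement; section 2.24-style detail aside, screening is assigned in section 2.10 to rehabilitation physicians, a different role. A random pick from opaque envelopes by an independent person does not let a recruiter foresee the next arm.
- **No sequence exists.** A random-number table is generated and enrolment order is mentioned. The wording may be loose English for handing out the randomised envelopes. It is contradictory, but it does not prove that there is no sequence.
- **The smallest arm would end with about 16 evaluable against 20 required.** Taking 80% of 19.9 does give about 16, but the fair comparator is 19.2, and the figure ignores the larger arms. The power figures are the better measure of the cost.

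Sealing, sequential numbering and custody of the list are details that an article may leave to the full protocol, so their absence is not counted here.

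**Conclusion.** The point holds as a mismatch between the planned arm sizes and the named method, together with an unclear allocation sentence. The arm-size probabilities are exact and rest only on 72 participants and unrestricted 1:1:1 allocation. The power figures rest on an assumed effect (90% at 20 v 20), a two-sided t-test and equal 80% retention, because the article gives no means or SDs. The typical cost is negligible; the risk lies in a draw that leaves one contrast clearly weaker than planned. The trial's validity is not in question on this ground, and neither a concealment failure nor selection bias has been shown. It should be corrected because the remedy is cheap.

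**What to change.** Replace simple randomisation with a computer-generated permuted-block list at 1:1:1, using randomly varying blocks of 3 and 6 with the sizes withheld from recruiters. If the blocks are complete at 72, the split is exactly 24/24/24. Reword the envelope sentence so that envelopes are assigned strictly in list order as participants enrol.

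Section 2.3 gives a study period of December 2021 to December 2022, so allocation may already have taken place. In that case, state the procedure actually used and the resulting arm sizes.

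The cost is a different list and one corrected sentence. The downside is slightly more predictability at the ends of blocks, which varying and concealing the block sizes limits.

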### 2.13. Ethics and dissemination

The trial will be conducted in accordance with the Declaration of Helsinki. The trial protocol was approved by the Biomedical Ethics Committee of West China Hospital, Sichuan University (No: 2021-1642). The study was registered in the Chinese Registry website (registered in ChiCTR.org with the identifier ChiCTR2200059255). Before the start of the trial, the researchers will explain the trial protocol to the participants, inform them of the benefits and risks of the trial, and obtain the participants’ written informed consent. Participants can withdraw from the trial at any time during the trial. The results of this trial will be shared with each participant and will be presented at national or international conferences, and papers will be submitted to peer-reviewed journals.

### 2.14. Statistical analysis

Analyses will use an intention-to-treat analysis strategy. We will use one-way ANOVA to determine baseline comparability between groups for quantitative variable data. Baseline comparability between groups of categorical variable data will be determined using the chi-square test or other suitable nonparametric tests. Quantitative data will be expressed as the mean; if it follows normal distribution and homogeneity of variance, otherwise median is given. In statistical inference, if the data obeyed a normal distribution, and homogeneity of variance and satisfied spherical symmetry, repeated measures data analysis of variance was used; if the data did not obey a normal distribution or the variance was unequal, the Kruskal–Wallis H rank sum test was used for data analysis. SPSS (V21.0) will be used for data analyses. We considered *P* ≤ .05 to be statistically significant.

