### 2.8. Outcome measures

Outcomes for the trial will be chosen based on Osteoarthritis Research Society International recommendations.^[43]^ Table 1 summarizes the primary and secondary outcome measures. Outcomes will be measured at baseline (T_0_) and at 4 (T_4_), 8 (T_8_) and 12 (T_12_) weeks after the allocation (Table 2).

**Table 1 T1:** Outcomes of this study.

Measurements	Metric of measurement	Method of measurement	Time point of primary interest
Primary outcomes			
Self-reported pain	0–20 (higher scores indicate more serious pain)	Western Ontario and McMaster Universities osteoarthritis index (WOMAC) – pain subscale	baseline, and 4, 8, and 12 wk after allocation
Secondary outcomes			
Self-reported pain	0–10 (higher scores indicate more serious pain)	Numerical pain rating scale (NRS)	baseline, and 4, 8, and 12 wk after allocation
Quality of life	Standardized scores for every section (higher scores indicate more better social participation)	The MOS item short from health survey (SF-36)	
Self-reported function and stiffness	0–76 (higher scores indicate more serious dysfunction)	WOMAC – physical function and stiffness subscale	
Functional performance	Seconds (shorter time indicates better function)	Timed up and go test	
Adherence	0–100% (Higher ratios indicate better adherence)	The ratio of the number of completed HXCR sessions to the total number of sessions	12 wk after allocation

HXCR = Huaxi Cloud Rehabilitation, NRS = numerical pain rating scale, SF-36 = The MOS item short from health survey, WOMAC = Western Ontario and McMaster Universities Osteoarthritis index.

**Table 2 T2:** The participant timeline.

Time point	Study period				
	Enrolment	Allocation	Post-allocation		
	−T_1_	0	T_4_	T_8_	T_12_
Enrolment					
Eligibility screening	×				
Informed consent	×				
Allocation		×			
Interventions					
Education					
Medication					
Exercise					
Assessment					
Sociodemographic data	×				
Personal and medical history	×				
IPAQ Short	×				
Primary outcome			×	×	×
Secondary outcomes			×	×	×

IPAQ Short = International Physical Activity Questionnaire.

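### Section 2.14 names no adjustment for baseline WOMAC pain and leaves the role of T0 in the repeated-measures model open; prespecified baseline adjustment would usually add power from data already planned.

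*Protocol article*

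**What the plan says.** All references are to the protocol article.

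- **Baseline data (2.14).** "We will use one-way ANOVA to determine baseline comparability between groups for quantitative variable data". Categorical variables get a chi-square or other nonparametric test.
- **Inference (2.14).** Repeated-measures ANOVA is used if normality, equal variance and sphericity hold. Kruskal-Wallis is used if normality or equal variance fails. No covariate is named, and the time levels of the ANOVA are not listed.
- **Baseline pain is planned.** Section 2.8 states "Outcomes will be measured at baseline" and at weeks 4, 8 and 12. The abstract and Table 1 agree. Section 2.11 (Randomization and blinding) states "After baseline measurement, participants will be randomized 1:1:1".
- **Table 2 ("The participant timeline")** marks the primary and secondary outcomes at T4, T8 and T12 only.
- **Sample size (2.9).** "the degree of reduction in WOMAC pain scores was used as an index", so the trial is sized on change from baseline. The target is stated "for a significance level of 0.05 and a yielding power of 90" per cent; "the sample size consists of 20 participants in each group". "With a 20% dropout rate taken into account, each group needs 24 enrolled participants".

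**The concern.** In a randomised trial, a significance test of baseline differences asks only whether chance produced them, and nothing in the plan depends on the answer. Baseline pain is more useful as a covariate, because it usually predicts later pain and so removes variance from the comparison. Section 2.14 does not use it that way, and the Kruskal-Wallis fallback cannot.

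What is at stake is precision in a small trial of about 20 evaluable participants per arm, allocated by simple randomisation. If the three baseline means have standard error 1 SD/√n, the chance that at least two of them differ by more than 0.5 SD is about 25% at 20 per arm and 19% at 24.

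Separately, Table 2 disagrees with the rest of the article on whether the outcomes are measured before allocation.

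**Working it through.** **The plan's own figure.** The formula in 2.9 needs three means and three SDs, which the article cites but does not print, so 20 per group cannot be reproduced. Solving backwards with the noncentral F distribution (three groups, alpha 0.05, power 90%) gives a standardised effect f = 0.472. For dropout, 20 × 1.2 = 24 matches the stated figure, and 24 × 0.8 = 19.2 remain per group.

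**Assumptions, none of them in the documents.** 20 per arm; both exercise arms 0.8 SD better than control at week 12; the same correlation r between all visits; r from 0.3 to 0.7. The reliability coefficient of 0.90 in 2.8.1 is not a 12-week correlation, and the NRS 3 to 6 entry range may lower r.

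**Week 12, like for like.** With means 0, 0.8 and 0.8, the sum of squares about their mean is 0.4267. The noncentrality is 20 × 0.4267 = 8.53, and power on (2, 57) df is 72%. ANCOVA multiplies the error variance by 1 − r² and uses 56 df. The last column is from 20,000 simulated trials per r, which also count the small loss from chance imbalance in the covariate.

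| r | 1 − r² | ANCOVA noncentrality | Power, formula | Power, simulated |
|---|---|---|---|---|
| 0 | 1.00 | 8.53 | 72% | 72% |
| 0.3 | 0.91 | 9.38 | 77% | 75% |
| 0.5 | 0.75 | 11.38 | 84% | 84% |
| 0.7 | 0.51 | 16.73 | 95% | 95% |

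The gain is about 3, 11 and 23 points at r of 0.3, 0.5 and 0.7. At r = 0 the simulated cost is about 1 point (72.6% to 71.6%). Kruskal-Wallis on week-12 scores has about 69-70%.

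**At the effect implied by 2.9.** With f = 0.472 (90% unadjusted), the formula gives ANCOVA 92.6%, 96.5% and 99.6% at r of 0.3, 0.5 and 0.7 if the 90% refers to follow-up scores (variance ratio 1 − r²). It gives 98.3%, 96.5% and 94.2% if the 90% refers to change scores (ratio (1 + r)/2).

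**If T0 is a time level and the group main effect is read.** Take a constant effect from T4 to T12, with the mean of the three follow-ups set to 90% power. Averaging in T0 leaves 3/4 of the effect. Variance per squared effect is:
- four-visit mean: [(1 + 3r)/4]/0.75²
- mean of three follow-ups: (1 + 2r)/3
- the same mean adjusted for baseline: (1 + 2r)/3 − r²

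At r = 0.5 these are 1.111, 0.667 and 0.417. Power at r of 0.3, 0.5 and 0.7 is 72%, 69% and 68% for the main effect with T0, and 94.7%, 98.6% and about 100% for the adjusted mean.

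**If T0 is a level and group-by-time is read.** The noncentrality is 8.53 × Σ(wⱼ − w̄)²/(1 − r) on (6, 171) df, where wⱼ is the share of the effect present at visit j. The sum is 0.556 for linear onset and 0.75 for full effect from T4. The comparator is the week-12 ANCOVA (formula values).

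| Onset | r | Group-by-time | Week-12 ANCOVA |
|---|---|---|---|
| Linear | 0.5 | 60% | 84% |
| Linear | 0.7 | 85% | 95% |
| Immediate | 0.5 | 75% | 84% |
| Immediate | 0.7 | 95% | 95% |

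**Chance imbalance.** If two arms differ by d at baseline, the expected error in their difference is r·d for follow-up scores, −(1 − r)·d for change scores and zero for ANCOVA. With d = 0.5 SD and r = 0.5, that is 0.25 SD in one direction or the other without adjustment.

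**The case against.** The strongest defence has four parts.

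- **Repeated-measures ANOVA is a valid test, and covariates are often left to a SAP.** The first half stands: this is a matter of efficiency, not validity. The second half does not remove the point, because the article goes beyond silence. It names the full method, including a fallback that cannot take a covariate.
- **Baseline may already be in use.** A reader might infer that baseline serves only for the comparability test, or alternatively that T0 is one of four repeated responses. Section 2.14 supports neither, since it lists no time levels. The sample size also rests on change, so baseline is not ignored.
- **Imbalance need not pass straight into the estimate.** A reader might infer that it does. If group-by-time is read, a constant baseline difference cancels from the changes, although regression to the mean then leaves an error of the opposite sign. How much error arises depends on r and on the term read.
- **The power loss can be exaggerated.** With linear onset and r = 0.5, the four-visit main effect has about 34% power and week-12 ANCOVA about 84%. A reader might call that gap the gain from adjustment. It also reflects a change of estimand and the assumed onset. With immediate onset the same main effect has about 67%, and the like-for-like week-12 gain is about 11 points.

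On Table 2, a reader might infer that baseline outcomes will not be collected. The abstract, 2.8, Table 1 and 2.11 all say otherwise, and the empty intervention rows may be a fault of text extraction. The rows for demographics, history and IPAQ do keep their enrolment marks, so the missing mark is a contradiction to reconcile and nothing more.

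**Conclusion.** The point holds as an improvement to the analysis. Section 2.14 states no baseline adjustment, does not fix the role of T0, and plans significance tests of baseline balance that inform nothing.

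Under the stated assumptions, adjustment adds about 3, 11 and 23 points of week-12 power at r of 0.3, 0.5 and 0.7, and costs about 1 point if r is zero. Compared with a group-by-time test, the advantage ranges from clear (linear onset, r = 0.5) to close to nil (immediate onset, r = 0.7). The documents give neither r nor the effect size nor the onset pattern, so the direction is firm and the size is a range. The article does not support a claim that the planned test is invalid, or that baseline pain will go uncollected.

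**What to change.** 1. In 2.14, analyse WOMAC pain at T4, T8 and T12 with a mixed model, or week 12 with ANCOVA, with baseline WOMAC pain as a prespecified covariate and T0 not among the responses. Treat each secondary outcome that has a baseline value in the same way; adherence has none.
2. Let this model replace both the repeated-measures ANOVA and the data-driven switch to Kruskal-Wallis, which cannot carry the covariate.
3. Report baseline data by group descriptively and drop the significance tests.
4. In Table 2, add the baseline mark for primary and secondary outcomes measured at baseline, so that it agrees with the abstract, 2.8, Table 1 and 2.11 (Randomization and blinding).

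The cost is rewording in 2.14, one correction in Table 2 and one degree of freedom for the covariate. No new data or participants are needed. The change should be made before any unblinded outcome data are seen.

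### Checks of normality and equal variance on the trial data decide which hypothesis the primary analysis tests; the fallback is not fully defined and one outcome of the checks has no analysis.

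*Protocol article*

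**What the plan says.** Section 2.14 of the protocol article holds the only inferential rule in the document. The first branch reads: "if the data obeyed a normal distribution, and homogeneity of variance and satisfied spherical symmetry, repeated measures data analysis of variance was used". The second reads: "if the data did not obey a normal distribution or the variance was unequal, the Kruskal–Wallis H rank sum test was used". No test or threshold is given for judging the assumptions. The section does not say which effect of the repeated-measures model is primary, which visit the rank test uses, or whether raw scores or changes from baseline are ranked. It mentions no baseline adjustment in either branch.

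Other sections do not settle this. Table 1 gives all four assessments (baseline, 4, 8 and 12 weeks) as the time point of primary interest for WOMAC pain. Section 2.9 sizes the trial on change: "The literature was reviewed to obtain the means and standard deviations of changes in pain scores in the three groups of patients with KOA". That hints at a change score, but section 2.14 does not take it up.

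**The concern.** The two branches do not answer the same question. Repeated-measures ANOVA asks whether the arms differ on average or in their course over the visits. Kruskal–Wallis asks whether one value per person has the same distribution in three independent groups. If the data decide between them, the primary hypothesis cannot be named before the data are seen. The analyst also keeps a free choice of visit and variable once the fallback applies.

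The remedy does not fit one of its two triggers. The null hypothesis of Kruskal–Wallis is equal distributions, so with unequal spread it is no longer a test of location alone.

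The rule is also incomplete. The first branch requires sphericity, but the second is triggered only by non-normality or unequal variance.

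**Working it through.** **Logic of the rule (no assumptions needed)**

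| Normal | Equal variance | Spherical | Analysis under 2.14 |
|---|---|---|---|
| yes | yes | yes | repeated-measures ANOVA |
| no | any | any | Kruskal–Wallis |
| any | no | any | Kruskal–Wallis |
| yes | yes | no | none stated |

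**Inputs from the document.** Three arms; four assessments (section 2.8); WOMAC pain as an integer score from 0 to 20 (section 2.8.1); significance at 0.05 (section 2.14); 20 evaluable per arm, 24 enrolled (section 2.9). The 20 cannot be recomputed, because the means and SDs behind it are not given. It is taken as it stands and is not disputed here.

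**How often the switch fires by chance.** The pre-tests are not named, so three rules were tried. Each test is at 5%, and any failure triggers the switch. If k tests were independent, the chance of at least one failure with exactly normal, equal-variance data would be 1 − 0.95^k. The simulation allows for dependence between tests, with an assumed equal correlation between visits of 0.5 to 0.7.

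| Assumed rule | k | 1 − 0.95^k | Simulated |
|---|---|---|---|
| Shapiro–Wilk on pooled residuals + Levene, week 12 | 2 | 9.8% | about 8–10% |
| Shapiro–Wilk per arm + Levene, week 12 | 4 | 18.5% | 17–20% |
| Shapiro–Wilk per arm and visit + Levene per visit | 16 | 56.0% | 51–55% |

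Under the third rule, rounding normal scores to the 0–20 integer scale (assumed mean 8, SD 3) raises the rate to about 66%.

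**Power of each branch.** Assumptions: normal data, 20 per arm, both exercise arms 0.8 SD better than control at week 12, effect building up linearly (0, 1/3, 2/3, 1 over the four assessments), equal correlation ρ between visits.

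Between-arm term: the arm means −0.8, −0.8 and 0 deviate from their average by −0.267, −0.267 and 0.533. The squares sum to 0.4267, and 20 × 0.4267 = 8.53.

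- Group-by-time F test of repeated-measures ANOVA: 6 and 171 df. The squared deviations of the time profile from its mean sum to 0.5556, so the noncentrality is 8.53 × 0.5556/(1 − ρ) = 9.5, 11.9 and 15.8 at ρ = 0.5, 0.6 and 0.7.
- ANCOVA of week 12 on baseline: 2 and 56 df; noncentrality 8.53/(1 − ρ²) = 11.4, 13.3 and 16.7.
- Kruskal–Wallis: by simulation.

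Simulated power:

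| ρ | Repeated-measures ANOVA, group-by-time | Kruskal–Wallis, raw week 12 | Kruskal–Wallis, change | ANCOVA, week 12 |
|---|---|---|---|---|
| 0.5 | 60% | 70% | 70% | 84% |
| 0.6 | 71% | 70% | 80% | 89% |
| 0.7 | 84% | 69% | 90% | 95% |

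The noncentral F distribution with the noncentralities above agrees with the two F-test columns to within about one point.

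**Agreement of the branches and type I error.** A further simulation assumed SD 3, baseline mean 9 and ρ of 0.5 or 0.7, with either 2.5 points of benefit in both exercise arms or 3 and 1.5 points. The group-by-time test and Kruskal–Wallis at week 12 reached different verdicts in 16–34% of trials with a true effect and in 8–10% under the null. With Kruskal–Wallis fixed at week 12, the two-branch rule had a type I error of 4.3–5.6%, close to nominal. If Kruskal–Wallis were run at each of the three follow-up visits and any significant result counted, the error was 10–14%.

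**The case against.** A reader might infer four stronger things from section 2.14. The document does not support them.

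- **That the switch inflates false positives.** The simulation does not show this for the switch alone. Inflation appears only if the fallback is repeated across visits and any success counts. The text does not exclude that, but does not plan it either.
- **That the switch lowers power.** The large gap, about 70% against 84–95%, is between Kruskal–Wallis on raw scores and a baseline-adjusted analysis, which the plan does not contain. Against the repeated-measures test actually planned, Kruskal–Wallis on week-12 scores is stronger at ρ = 0.5, about equal at 0.6 and weaker at 0.7. Most of the gap to ANCOVA comes from the missing baseline adjustment, not from ranking.
- **That the fallback ignores baseline.** This would hold for raw scores. Ranking changes would use baseline, and section 2.9 is written in terms of change. Section 2.14 leaves the matter open.
- **That the switch would fire in half of all trials even with ideal data.** This needs 16 assumed pre-tests with any single failure counting. Simpler rules give 8–20%.

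It can also be said that a full analysis plan may name the pre-tests, the visit and a sphericity correction. That is fair for those details, and the gap for failed sphericity weighs less for that reason. It does not remove the main point: the article states a rule under which the data select between two different hypotheses. Filling in details would leave that rule in place.

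**Conclusion.** The point stands as a defect in a stated rule. The trial data decide whether the primary analysis is a group-by-time comparison over four visits or a rank comparison of one unspecified value per person, and one combination of assumption checks leads to no analysis. These conclusions follow from the wording alone.

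The harm is an undefined primary hypothesis, analyst freedom, and power that varies with the branch. The size is uncertain. By chance, the switch would fire in anything from about 8% to 55% of trials with exactly normal data, depending on the unnamed pre-tests, and in about 66% for an integer score under the widest rule. Neither inflated type I error from the switch alone nor a consistent loss of power against repeated-measures ANOVA is shown. Under the assumed effect and correlations, both branches fall short of a baseline-adjusted comparison at week 12, including when changes are ranked (70–90% against 84–95%). All percentages rest on the assumed pre-tests, correlation, effect size and linear build-up, none of which the document gives.

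**What to change.** Delete the switch from section 2.14 and fix one primary analysis that applies whatever any assumption check shows. One suitable choice is WOMAC pain at week 12 compared between arms with baseline as covariate, either by ANCOVA or by a mixed model over the visits with unstructured covariance, which needs no sphericity. If residuals look non-normal or variances unequal, keep the same contrast and report robust (sandwich) or bootstrap confidence intervals. Keep a rank-based test as a sensitivity analysis only, with its visit and variable named.

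Other single analyses would also remove the defect, provided that visit, variable and test are fixed in advance. The cost is rewording section 2.14 and slightly more analysis work. Recruitment, assessments and sample size are unaffected.
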